## Abstract

**Background:**

A healthy lifestyle program that appeals to, and supports, obese New Zealand (NZ) European, Māori (indigenous) and Pasifika men to achieve weight loss is urgently needed. In Scotland, Football Fans in Training (FFIT), a weight management and healthy lifestyle program for overweight and obese men aged 35–65 years , delivered by community coaching staff at professional football clubs, has been shown to be beneficial and cost-effective. A pilot program inspired by FFIT but delivered by professional rugby clubs in NZ (*n* = 96) was shown to be effective in weight loss, improved physiological outcomes, and adherence to healthy lifestyle behaviors in overweight and obese men. The objective of this trial is to determine the effectiveness and cost-effectiveness of the Rugby Fans in Training New Zealand (RUFIT-NZ) program.

**Methods:**

A pragmatic, two-arm, multi-center, randomized controlled trial involving 308 overweight and obese men aged 30–65 years, randomized to either an intervention group (*n* = 154) or a wait-list control group (*n* = 154). The intervention-group participated in the 12-week RUFIT-NZ program, a gender-sensitized, healthy lifestyle intervention adapted to the environment and cultural diversity of NZ and delivered through professional rugby clubs. Participants in the intervention group undergo physical training sessions, in addition to workshop-based sessions to learn about nutrition, physical activity, sleep, sedentary behavior, and a range of behavior-change strategies for sustaining a healthier lifestyle. The control group receives the program after 52 weeks. The primary outcome is change in body weight from baseline to 52 weeks. Secondary outcomes include change in body weight at 12 weeks; waist circumference, blood pressure, fitness, and lifestyle behaviors at 12 and 52 weeks; and cost-effectiveness. A process evaluation informed by the RE-AIM framework will evaluate potential implementation of RUFIT-NZ as an ongoing program in NZ after the trial.

**Discussion:**

This trial will investigate the effectiveness and cost-effectiveness of the RUFIT-NZ program in overweight and obese NZ men.

**Trial registration:**

Australia New Zealand Clinical Trials Registry, ACTRN12619000069156. Registered on 18 January 2019, according to the World Health Organization Trial Registration Data Set. Universal Trial Number, U1111-1245-0645.

## Background

High Body Mass Index (BMI), poor diet, and physical inactivity were ranked among the top-10 risk factors attributable to the global burden of disease in 2010 [1]. In New Zealand (NZ), 32% of adults are obese (BMI > 30 kg/m^2^) and a further 35% are overweight, with notable sex and ethnic disparities. Compared with women, the prevalence of overweight is greater in NZ men classified as NZ European/Other (41% vs 32%), Māori (the Indigenous peoples of NZ; 33% vs 27%), and Pasifika (26% vs 16%, respectively) [2]. Further, Māori and Pasifika men are 1.7 and 2.2 times more likely to be obese when compared with non-Māori and non-Pasifika men, respectively. Clearly overweight and obese NZ men, and in particular Māori and Pasifika men, are underserved by existing public health strategies [3, 4]. Healthy lifestyle programs that are both appealing to, and support, these men in weight loss and long-term lifestyle changes are urgently needed.

In the United Kingdom, Football Fans in Training (FFIT), a weight management and healthy lifestyle program, was developed to specifically target overweight and obese (BMI 28 kg/m^2^ or above) middle-aged men (aged 35–65 years) [5, 6]. FFIT was delivered via professional soccer clubs in Scotland, in an attempt to appeal to men, and draw on their fandom or allegiance to the clubs [7–9]. FFIT is evidence-based, gender-sensitized in context, content and style of delivery, includes behavior-change techniques known to be effective in promoting weight loss and physical activity [10, 11] and includes components designed to improve healthy eating, physical activity, and alcohol consumption [12]. A randomized controlled trial (RCT) of FFIT (*n* = 748) showed a mean difference in weight loss of 4.94 kg (95% CI 3.95–5.94) at 12 months [5]. After 3.5 years, 65% of the men had maintained a mean weight loss of 2.9 kg [13]. Since the original FFIT trial, there has been considerable interest in using professional sports clubs to encourage men to participate in a range of health promotion initiatives [5, 14–20]. Qualitative research has found that the social support received through participating in these sport-based lifestyle programs is highly valued by participants [21–23]. However, the type of support provided, and the extent to which participants gain a sense of identity with the program, have not been investigated.

In NZ, where a dominant rugby culture exists with large fan bases among NZ European, Māori and Pasifika people, we developed and piloted Rugby Fans in Training New Zealand (RUFIT-NZ), a program inspired by FFIT, but where professional football clubs were replaced with professional rugby clubs to harness sports club affiliation [8]. Formative work conducted prior to the pilot study sought to determine the level of cultural adaptation required to engage Māori and Pasifika men in NZ and to meet the needs of NZ men more generally. This resulted in some adaptations to the UK FFIT program for NZ, including a more holistic perspective of health or “*haoura”* in Māori [24], and changes to workshop sessions to include mindful eating, improving sleep, and reducing screen use and sedentary behaviors. Finally, for RUFIT-NZ, nutrition information was delivered by a nutritionist, reflecting men’s desires to receive dietary advice from someone with specialist knowledge [25].

A pilot RCT (*n* = 96) was conducted to evaluate the preliminary efficacy of RUFIT-NZ and to address feasibility issues including recruitment, retention, and acceptability of the program. After the 12-week intervention, a − 2.5 kg (95% CI − 0.4 to 5.4) difference in body weight was observed in favor of the intervention group. In addition, participants who received the program had significant reductions in waist circumference, resting heart rate, diastolic blood pressure, as well as improved fitness and improved adherence to lifestyle behaviors, including not smoking, and being physically active [25]. Furthermore, 100% of those who completed the program said that they would recommend it to their friends, therefore supporting the feasibility and acceptability of RUFIT-NZ, and supporting a larger-scale RCT of the program [25].

This paper describes the study protocol for the RUFIT-NZ main trial, which aims to determine the effectiveness and cost-effectiveness of RUFIT-NZ on weight loss and improvements in diet, physical activity, alcohol use, and in perceived social support at 52 weeks in overweight men aged 30–65 years. A secondary aim is to undertake an embedded process evaluation of RUFIT-NZ to assess reach, effectiveness, adoption, implementation, and maintenance outcomes [26, 27]. Two dimensions operate at the individual level (reach and effectiveness) Additional file 1.

## Methods

### Study design

RUFIT-NZ is a pragmatic, multi-center, two-arm, parallel RCT, which includes an embedded process evaluation framework (RE-AIM) to assess reach, effectiveness, adoption, implementation, and maintenance outcomes. *R*each refers to the proportion and characteristics of participants who receive the intervention. *E*ffectiveness concerns the impact of the intervention on the intended outcome. Adoption and implementation operate at the staff and organizational level. *A*doption refers to the percentage and characteristics of staff and settings that are willing to adopt or implement the intervention. *I*mplementation refers to the fidelity of implementing the intervention across settings and staff. *M*aintenance refers to the sustainability of the intervention once research support has ceased. This protocol has been prepared in accordance with the Standard Protocol Items: Recommendations for Interventional trials (SPIRIT) 2013 Statement [28] and is presented in Table 1. The SPIRIT Checklist is shown as Additional file 2. Further, the intervention is described according to the Consolidated Standards of Reporting Trials (CONSORT) Checklist [29, 30].

**Table 1 Tab1:**
[figure not shown]
The schedule of the Rugby Fans in Training New Zealand (RUFIT-NZ) study period including; enrollment, interventions, and assessments

### Study setting

RUFIT-NZ is based within professional rugby clubs who participate in the Super Rugby competition across NZ (currently The Blues rugby club based in Auckland (North Island), The BNZ Crusaders based in Christchurch, and the Pulse Energy Highlanders based in Dunedin (both in the South Island)).

### Study population and recruitment

Eligible participants are men aged 30–65 years who are overweight (defined as a BMI of ≥ 28 kg/m^2^), able to safely undertake physical activity, can understand and read English, and are able to provide written informed consent to participate in the study. All participants are pre-screened using the Physical Activity Readiness Questionnaire (PAR-Q) [31, 32] with physician consent to participate required for all participants endorsing any PAR-Q items. Participants are excluded if they are participating in another healthy lifestyle program or know at baseline that they will be unable to complete the 1-year follow-up. Participants are recruited via the respective club’s fan base registries, including their Facebook pages, supporter mailing lists, and newspaper advertisements/articles; they are also recruited through Māori-specific networks (via *Marae* and media (e.g., Māori television and radio)) and Facebook advertisements.

Each advertisement links to the University of Auckland’s Faculty of Medical and Health Science’s research study recruitment page. Using this page, participants access additional information about the study, the Participant Information Sheet/Consent Form, and have the option of contacting the research team for further information or linking directly to the online plan and registration form. As part of the screening questionnaire, participants confirm that they can attend one of the pre-specified baseline assessments located at their preferred rugby club, and complete the PAR-Q [31]. Participants are reminded to bring a letter to the baseline assessment from their general practitioner (GP) confirming that it is safe for them to exercise and participate in the study (if required). Once the online self-report screening questionnaire is complete, eligible participants are asked to select the pre-determined day and time that they would prefer to come to the club to complete their baseline measurements. During the baseline assessment and following collection of their weight and height, and calculation of BMI, participant eligibility is confirmed (see Additional file 3).

### Sample size

A total of 308 participants (154 per arm) will provide 90% power at 5% significance level (two-sided) to detect a clinically significant 5-kg difference [7] on the primary outcome between the two groups at 52 weeks, assuming a standard deviation (SD) of 12 kg allowing for 20% loss to follow-up. Our SD is conservative and was derived from similar weight management trials for men [25, 33]. Based on the pilot study, the proposed 5-kg difference in body weight would be similar to a reduction in body mass of between 4 and 5% [25]. As the indigenous population in NZ, we aim to recruit a total of 150 Māori participants (~ 50% of the total sample size), which would provide 80% power to detect a 6-kg difference between groups under the same assumptions. Each club will implement strategies to minimize loss to follow-up and improve retention throughout the intervention (i.e., encouraging attendance, trainers notifying the coordinating center if men are absent for more than 2 weeks in a row with no explanation, and social media groups that all the men join) and for the follow-up testing sessions (i.e., provide the men with club merchandise where available, have club players present at the session, and offer alternate session times if required). As part of the consent process, participants are informed that they may withdraw from the program at any time during the study, without providing a reason to the research team or club.

### Randomization

Following baseline data collection, eligible and consented participants are randomized to either the RUFIT-NZ intervention or the control group in a 1:1 ratio using a computerized randomization process, ensuring allocation concealment. Randomization is stratified by baseline BMI category (< 35 kg/m^2^ vs ≥ 35 kg/m^2^), self-reported ethnicity (Māori, Pasifika, non-Māori/non-Pasifika), and study center, using stratified block randomization with variable block sizes of 2 or 4. Participants are informed by email of their eligibility and allocation group within 2–3 days of their baseline assessment at the club. Due to the nature of the study, participants and research assistants will be aware of the treatment allocation post randomization. Study investigators and trial statistician will remain blinded until the end of the trial. To reduce assessment bias, the primary and key secondary outcomes will be measured objectively at 12 and 52 weeks.

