#### Fitness (baseline, 12- and 52-week follow-ups)

Assessed by a 6-km cycle test, a timed sit-to-stand test, and a timed push-up test.

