### Data collection and management

All self-reported data are directly input via online surveys to the web-based data capture system Research Electronic Data Capture (REDCap) [52, 53] hosted at the National Institute for Health Innovation (NIHI). All objective data are collected on hardcopy at face-to-face sessions by trained researchers and then input to the same REDCap web-based data capture system hosted and managed at NIHI. At least two measurements are completed for each of the anthropometric and blood pressure measures. Anthropometrics, blood pressure and fitness testing data were collected by trained research assistants. All data are kept for 6 years and will only be used in future studies following a process of participant informed consent.

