### Fidelity

Intervention fidelity is evaluated by means of direct observation by trained research assistants, using a standardized checklist at weeks 4 and 10 of the 12-week intervention. Feedback will be provided by the research team to the trainers to address any gaps in intervention delivery.

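### Research assistants who may know the allocation take all anthropometric, blood pressure and fitness measurements, and objective measurement is weak protection for waist, manual blood pressure and fitness

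*Protocol article*

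**What the plan says.** The Randomization section of the protocol article says that, because of the nature of the study, "participants and research assistants will be aware of the treatment allocation post randomization". Blinding is kept for two other groups: "Study investigators and trial statistician will remain blinded until the end of the trial". The same section then gives its protection against biased assessment: "To reduce assessment bias, the primary and key secondary outcomes will be measured objectively at 12 and 52 weeks". It does not name the key secondary outcomes.

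Data collection and management says who takes the measurements: "Anthropometrics, blood pressure and fitness testing data were collected by trained research assistants". It divides the data into two classes. One is self-report: "All self-reported data are directly input via online surveys to the web-based data capture system". The other is everything measured in person: "All objective data are collected on hardcopy at face-to-face sessions by trained researchers". It also requires at least two readings of each anthropometric and blood pressure measure.

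The outcome sections specify calibrated digital scales for weight, a tape for waist, and an automated or manual device (or both) for blood pressure. Fitness is "Assessed by a 6-km cycle test, a timed sit-to-stand test, and a timed push-up test". Under Fidelity, intervention sessions in weeks 4 and 10 are checked by "direct observation by trained research assistants".

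**The concern.** Participants in a wait-list trial of a group program must know their arm. The staff who run a tape around them or time an exercise test need not. Randomization is computerized, the men are told their allocation by email, and club trainers and nutritionists deliver the program. No measurement task described in the article requires knowledge of the arm.

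The plan therefore relies on the character of the measurements rather than on blinding. That works where an instrument produces the reading. It works less well where the assessor places a tape, reads a manual blood pressure device, or conducts a test whose result depends on how hard the man tries. An unconscious tendency to favor the program would pass directly into the between-group differences in waist, blood pressure and fitness at 12 and 52 weeks. The abstract lists all three as secondary outcomes. Neither adjustment for baseline nor multiple imputation would remove such a shift, because it arises after randomization and differs by arm.

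**Working it through.** **Step 1. Who measures, and what they know.** Randomization says research assistants are aware of allocation. Data collection and management says research assistants take the anthropometric, blood pressure and fitness measurements. The article mentions no separate blinded assessor. Taken together, every in-person outcome is measured by a staff group that is allowed to know the arm.

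**Step 2. How far objective measurement protects each outcome.**

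| Outcome | How obtained | Exposure to an assessor who knows the arm |
|---|---|---|
| Weight (primary) | Calibrated digital scales, at least two readings | Little |
| Blood pressure, automated | Automated device, at least two readings | Little |
| Blood pressure, manual | Manual device, at least two readings | Some: assessor reads the value |
| Waist | Tape, at least two readings | Some: placement and reading |
| Fitness | 6-km cycle, timed sit-to-stand, timed push-up; not covered by the duplicate-reading rule | Some: effort and conduct of the test |
| Lifestyle behaviors | Self-report, entered online | None from assessors |

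Duplicate readings by the same person reduce random error. A tendency common to both readings survives averaging.

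**Step 3. The number analysed per arm.** The plan's own sample size is reproduced first. Inputs from Sample size: difference 5 kg, SD 12 kg, two-sided 5%, power 90%, 20% loss.

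- Normal approximation: n = 2 × (1.960 + 1.282)² × (12/5)², about 121.1, rounded up to 122 per arm.
- With the t distribution: 122.01, rounded up to 123 per arm.
- Allowing for loss: 123/0.8 = 153.75, rounded up to 154 per arm, 308 in total. This matches the plan.

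So 123 per arm is the number the plan expects to analyse.

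**Step 4. Illustration of what a shift would do.** Assume there is no true effect and the assessors shift the intervention arm by b standard deviations. Here SD means the residual SD of the comparison being tested. The document gives no value for b; 0.1 and 0.2 are assumptions.

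- Standard error of the difference = √(2/123) = 0.1275 SD.
- Expected z = b/0.1275.
- Chance of p < 0.05 = 1 − Φ(1.96 − z) + Φ(−1.96 − z).

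| Assumed shift b | Expected z | False-positive rate |
|---|---|---|
| 0 | 0 | 5.0% |
| 0.1 SD | 0.784 | 12.3% |
| 0.2 SD | 1.569 | 34.8% |

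**Step 5. Can anything still be changed?** Trial status reports recruitment from January 2019 and 200 men randomized by 21 June 2019. The earliest 52-week visit falls in January 2020, so none was due at that date. Men randomized by 29 March 2019 (12 weeks before 21 June) would already have reached their 12-week visit.

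**The case against.** The strongest defense is that the article discloses the lack of blinding and claims only to reduce assessment bias, not to remove it. It uses the word objective in contrast to self-report, and in that sense a tape and a stopwatch are objective. Assessors are trained, anthropometric and blood pressure readings are duplicated, and the statistician is blinded. The primary outcome is hard to bias. All of this is fair. The point is therefore a judgment that the safeguard is weak for some outcomes, not that the text contradicts itself.

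Three stronger readings are tempting, and the article does not support them:

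- A reader might infer that unblinded staff take every outcome measurement. They do not, because self-reported outcomes go directly into online surveys.
- A reader might infer that the same assistants watch the intervention sessions and later measure those men. The article uses the same job title for both tasks but does not say that the same individuals do them.
- A reader might infer that the fitness scores rest on assessors counting repetitions or urging men on. The article says only that the tests are timed, or are a cycle test over a fixed distance.

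It is also true that test scripts, form layout and rosters normally sit in an operating manual, so their absence from an article is no fault. The fault is the positive statement that assistants will know the allocation, supported by a reason that applies only to participants.

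Finally, the shifts in the illustration are not evidence about this trial. Any trial of this size would give the same figures.

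**Conclusion.** The point holds for waist, manual blood pressure and fitness. For these, the plan lets the people who measure know the arm, gives no reason that applies to them, and relies on a safeguard that is weak for these measures. The conclusion on weight is little affected, and self-reported outcomes are not affected by assessor knowledge.

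The size of any bias is unknown. If it were 0.1 to 0.2 residual SD in favor of the program, the false-positive rate of a single secondary comparison would be about 12% to 35% instead of 5%, with 123 analysed per arm. This assumes a uniform shift in one direction and no true effect. The result does not depend on the same staff observing sessions and measuring outcomes; such overlap would only add to the exposure. It is a weakness worth correcting for secondary outcomes, not a threat to the primary analysis.

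**What to change.** For 12- and 52-week visits not yet done, with existing staff:

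1. Do not release allocation to the assistants who take the measurements.
2. Use recording forms that show neither allocation nor earlier readings.
3. Ask the men not to disclose their arm at the visit.
4. Use the same standardized instructions and encouragement in both arms for waist, blood pressure and fitness.
5. Where current staffing allows, do not have an assistant who observed fidelity sessions measure the same men. The article does not give staff numbers by center, so this step cannot be assumed free everywhere.

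In the Randomization section, limit the claim of protection from assessment bias to weight on digital scales and automated readings. In the trial report, state that waist, manual blood pressure and fitness measured by staff aware of allocation are open to assessor bias, and say which visits this covers.

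The cost is some scheduling effort and a change to forms and instructions. The sample size and visit schedule stay as they are. Blinding will be imperfect because men may disclose their arm, and nothing can be done for visits already completed or for assistants who already know the allocation.

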### Intervention

Specific details of the RUFIT-NZ program and how it was developed have been reported elsewhere [25]. In short, RUFIT-NZ is a 12-week healthy lifestyle program, consisting of 12 × 2-h sessions. Each intervention session includes a 1-h workshop-based education component (see Table 2) and 1-h group-based but individually tailored exercise training session. The education component aims to introduce participants to theory-based behavior-change techniques and to a range of topics relating to nutrition, sleep, alcohol consumption, and physical activity. The content of the classroom sessions has been standardized, so that the men participating at all clubs receive the same topic and key delivery points, but each club is able to tailor the sessions for delivery.

**Table 2 Tab2:** The content of each workshop in the Rugby Fans in Training New Zealand (RUFIT-NZ) program

Week/session	Topics/core messages to cover	Facilitator
Week 1: Lifestyle approach to health and goal-setting	• Welcome and getting to know each other • Focus on lifestyle behaviors vs weight • SMART goal-setting • Team photo	Trainer
Week 2:*“Big wins” – nutrition*	• Whole food philosophy including social aspects • Big wins for healthy diets • Incorporating fruit and vegetables • Healthy drink options • Healthy serving sizes • Reading food labels	Nutritionist
*Week 3: Planning and budgeting – nutrition*	• Menu-planning • Budgeting • Shopping • Being organized/importance of routine	Nutritionist
Week 4: Behavior change	• Discussion of important behavior-change techniques: autonomous motivation, building confidence, goal setting, action and coping planning, self-monitoring, social support	Trainer
Week 5: *Mindful eating – nutrition*	• Focusing on your “circle of influence” • Eating out – mindful eating	Nutritionist
Week 6: Injury prevention	• Informal session designed by trainer to meet individual needs of men in team	Trainer/physio
Week 7: *Q & A – nutrition*	• Q & A session	Nutritionist
Week 8: Alcohol and health	• Alcohol weight-related facts • Standard drink sizes • Planning your drinking	Trainer
Week 9: Q & A (physical activity)	• Q & A session	Trainer
Week 10: Sleep and sedentary behavior	• How sleep affects weight • How much sleep we need • Signs of sleep deprivation • Sleep hygiene tips • What is sedentary behavior • How SB affects weight • Tips for reducing SB	Trainer
Week 11: Long-term behavior change and overcoming obstacles	• Importance of enjoying PA for long-term maintenance • Overcoming obstacles • Planning for lifestyle change • Relapse prevention	Trainer
Week 12: Team photo and motivational talk	• Wrap-up • Motivational talk • Team photo and certificate	Trainer

*SB* sedentary behavior, *PA* physical activity

Education sessions are delivered predominantly by RUFIT-NZ-trained trainers, with the exception of the nutrition-based components, which are delivered by the club’s nutritionist. RUFIT-NZ trainers are qualified strength and conditioning trainers involved with the respective rugby clubs.

With respect to the group-based in-stadia physical activity sessions, trainers are given the freedom to decide how to structure each of the sessions. This allows the trainers to decide how best to meet the needs of the individual men attending their specific RUFIT-NZ session. Each session progressively increases in difficulty over the 12 weeks, whilst taking account of each individual man’s levels of fitness and is designed to be fun and varied, utilizing the supportive group involvement to foster the sense of being in a “team.” The proposed group size ranges from approximately 15–20 men per trainer. Roll calls are taken at the beginning of each session to assess program attendance.

Throughout the intervention, men are encouraged to follow a daily step-based walking program [34–36]. All participants are encouraged to use a step counter (pedometer or smartphone app) to track their progress and receive a weekly step goal program to follow outside of the structured program. Furthermore, they are encouraged to do other forms of physical activity of their own choosing with a focus on integrating incidental activity into daily life (e.g., parking further from work). The RUFIT-NZ trainers also suggest “homework” physical activity that participants can do outside of the sessions. Participants’ lifestyle behaviors in terms of alcohol, sleep, sedentary behavior, and nutrition will be guided by individual goals, which men set for themselves during the group education sessions and record in a workbook accompanying the program for their own reference.

The RUFIT-NZ nutrition-based content was developed by our investigator nutritionist [name], and is delivered using a Family, Activity, Behavior (FAB) approach [37]. However, because the diets of participants are influenced by their partners, family members (*whanau*) and friends, and the environment in which they live, learn, work, and play, the focus is on dietary changes that each participant can make within his own unique ‘circle of influence’ [38]. The nutrition sessions are positively framed (e.g., “what are some good examples of healthy snacks?” and “where can I find quick easy recipes?”). Information is delivered via simple messages focusing on the practical elements of improving diet, and where possible is food – rather than nutrient-focused. RUFIT-NZ nutrition sessions target the biggest “wins” for a healthy diet, considered to be:
Eating as many fruit and vegetables as possibleCooking and preparing food and snacks at home as much as possibleEating mostly whole foods (as opposed to packaged/processed foods and takeaways)Drinking sugar-free beveragesConscious eating (screen-free, mindful eating, ideally in the company of others)

By focusing on these positive behaviors participants will, by default, consume less fast food, sugar-sweetened beverages, alcohol, energy, salt, sugar, and smaller portion sizes, reduce their risk of common nutrition-related diseases, and hopefully reduce their body weight. The men are also provided with a food diary to record their diet should they wish during the intervention. These messages also align with the NZ Eating and Activity Guidelines for Adults [39].

